## Abstract

**Background:**

Colorectal cancer (CRC) is the second most prevalent type of cancer in the world. Surgery is the only curative option. However, postoperative complications occur in up to 50% of patients and are associated with higher morbidity and mortality rates, lower health related quality of life (HRQoL) and increased expenditure in health care. The number and severity of complications are closely related to preoperative functional capacity, nutritional state, psychological state, and smoking behavior. Traditional approaches have targeted the *postoperative* period for rehabilitation and lifestyle changes. However, recent evidence shows that the *preoperative* period might be the optimal moment for intervention. This study will determine the impact of multimodal prehabilitation on patients’ functional capacity and postoperative complications.

**Methods/design:**

This international multicenter, prospective, randomized controlled trial will include 714 patients undergoing colorectal surgery for cancer. Patients will be allocated to the intervention group, which will receive 4 weeks of prehabilitation (group 1, prehab), or the control group, which will receive no prehabilitation (group 2, no prehab). Both groups will receive perioperative care in accordance with the enhanced recovery after surgery (ERAS) guidelines. The primary outcomes for measurement will be functional capacity (as assessed using the six-minute walk test (6MWT)) and postoperative status determined with the Comprehensive Complication Index (CCI). Secondary outcomes will include HRQoL, length of hospital stay (LOS) and a cost-effectiveness analysis.

**Discussion:**

Multimodal prehabilitation is expected to enhance patients’ functional capacity and to reduce postoperative complications. It may therefore result in increased survival and improved HRQoL. This is the first international multicenter study investigating multimodal prehabilitation for patients undergoing colorectal surgery for cancer.

**Trial registration:**

Trial Registry: NTR5947 – date of registration: 1 August 2016.

## Background

Colorectal cancer (CRC) is the second most prevalent type of cancer in the world, with over 1.4 million cases and 693.900 deaths a year [1]. The only way to cure this condition is by surgical removal of the tumor. However, postoperative complications occur in up to 50% of patients and they are associated with higher morbidity and mortality rates, increased expenditure on health care and poorer health related quality of life (HRQoL) [2–4]. Major surgery brings a 20 to 40% reduction in physiological and functional capacity, even in absence of complications [5]. This diminished reserve increases the level of fatigue up to months after hospital discharge [6]. Only 40% of patients return to their preoperative baseline functional capacity (as measured by VO2 peak). Moreover, a proportion of colorectal cancer patients are eligible for (neo)adjuvant which is known to further compromise functional recovery and survival [7, 8].

There is emerging evidence suggesting that many of the negative effects of major surgery can be reduced through the attenuation of surgical stress [9]. Efforts to improve the recovery process have primarily focused on the intraoperative factors (such as minimally invasive surgery and afferent neural blockade [10]) and postoperative interventions (examples being “fast track” early nutrition and mobilization [11]). The latter protocols have been designed to facilitate the return of functional activities and accelerate convalescence. However, the *postoperative* period may not be the best time to ask surgical patients to make significant changes in their nutrition and exercise since patients are tired and concerned about perturbing the healing process. As well as anxious about possible additional treatments for their underlying condition. The *preoperative* period may in fact be a better time to intervene in the factors that contribute to recovery, both physical and mental, and alleviate some of the emotional distress associated with the anticipation of surgery and the recovery process [12–14].

The process of improving the functional capacity of the individual in order to enable them to withstand an incoming stressor has been termed *prehabilitation* [15, 16]. Although some approaches have focused on education to prepare patients for procedures [17], few steps have been taken to systematically enhance functional capacity before surgery. With most studies performing single modal interventions only. To investigate the impact of preoperative exercise on the recovery of functional capacity after colorectal surgery, a few pilot studies have been performed which show promising results [14–16, 18, 19].

Subgroup analysis of the study of Carli et al., showed that patients whose functional exercise capacity improved preoperatively, recovered relatively well in the postoperative period - regardless of the exercise technique [20]. However, one-third of patients deteriorated preoperatively despite the exercise regimen, and these patients were also at greater risk of prolonged recovery after surgery. Poor preoperative physical function (fatigue, malnutrition and physical performance) and the presence of anxiety and depression were also significant confounding predictors of prolonged recovery [21–25]. These results suggest that exercise training alone is not sufficient to attenuate the stress response in all patients and that it is also important to address factors such as nutrition and coping behavior that promote beneficial adaptation to training. Gillis et al. conducted a pilot study that showed that significant changes in postoperative functional exercise capacity can be achieved with a prehabilitation program [26]. However, they did not address the clinically relevant relationship between preoperative functional capacity (an increase of more than 20 m on the six-minute walk test (6MWT)), and the postoperative outcome (comprehensive complication index (CCI) reduction of 30%). If functional capacity can be improved preoperatively, we may expect a reduction in postoperative complications.

Since it has been established that the number and severity of complications are closely related to preoperative functional capacity, nutritional status, smoking behavior and psychological well-being, there has been increasing interest in targeting these issues with a multimodal intervention program [15]. From a physiological point of view and based on limited practical experience, it seems feasible to achieve clinically relevant effects during the period of 4–5 weeks between diagnosis and operation [14, 15, 27]. However, this can only be achieved with targeted interventions that include exercise, nutrition, stopping smoking, and psychological support.

### Study objectives

The general aim of this study is to investigate whether multimodal prehabilitation could enhance postoperative outcome using the CCI and 6MWT. Secondary outcomes will include patient reported outcome measures (PROMs) such as HRQoL and depression and anxiety scores, functional capacity measurements, nutritional and smoking status, length of hospital stay, study compliance, patients’ satisfaction and a cost-effectiveness analysis.

## Methods

This is an international multicenter, randomized controlled trial with two study groups. Written informed consent will be obtained from all patients. The trial will be conducted according to the rules of Good Clinical Practice and a Data Safety Monitoring Board (DSMB) has been appointed to monitor (serious) adverse events. The Netherlands Comprehensive Cancer Organisation will be responsible for quality control and data management. Ethical approval for this study was granted by the Medical Ethics Committee of the Máxima Medical Center (Veldhoven, the Netherlands) under reference number W16.100/NL58281.015.16. Important protocol modifications will be addressed to relevant parties.

### Study population

Adult patients (> 18 years) undergoing elective colorectal resection for cancer are eligible for inclusion. We will include 714 patients: 357 in each arm. We expect a dropout rate of 10% based on previous pilot studies. The estimated duration of the recruitment period is two years. Exclusion criteria are metastatic disease known preoperatively, paralysis or patients with mobility problems (who are unable to exercise), premorbid conditions or orthopedic impairments that contraindicated exercise, cognitive disabilities, chronic renal failure (dialysis or creatinine > 250 mmol), ASA score 4 or higher, and illiteracy (inability to read and understand the language of the country where the study will be performed).

### Randomization

Patients will be block randomized with a 1:1 allocation by means of randomization software (Research Manager clinical trial data management system, Deventer, the Netherlands), stratified by study sites, tumor location and neoadjuvant treatment. Patients will be allocated either to the intervention group, which will receive 4 weeks of prehabilitation, or to the control group, which will receive no prehabilitation.

In all participating centers, both the investigator and the surgeon responsible will verify eligibility. If the indication for surgery is established, patients will be screened by the medical research team for health conditions that prohibit participation in the program. They will then be called by the research investigator and an appointment will be made to provide written and oral information about the trial during a scheduled outpatient appointment. Patients will be given enough time to enquire about the details of the trial and to decide whether or not they wish to participate. Patients will be required to sign the informed consent form in the presence of the surgeon or investigator. A participant flow diagram is shown in Fig. 1. After the study has been explained and consent is obtained, there will be a multidisciplinary assessment. Based on intake by the sports physician, the physiotherapist/kinesiologist, the nutritionist and the case manager/psychologist, an individual prehabilitation program will be started during four weeks in the intervention group.

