### Statistical analysis

Baseline characteristics of both groups will be compared to assess the adequacy of the randomization. Data will be analyzed on an intention-to-treat basis. In addition, a per-protocol analysis will be performed. Trial results will be published in a respective journal. Primary and secondary outcomes for the intervention and control groups will be compared.

The primary outcome CCI will be described as the mean plus the standard deviation (SD). Since we expect CCI to be right skewed we will also describe CCI as the median plus interquartile range (IQR) and percentage above 20. To test the hypothesis (H0) that the study arms result in similar CCIs (in other words, prehabilitation does not prevent postoperative complications), we will use the Student’s T-test if data are normally distributed. Mann-Whitney U if data are not normally distributed or statistical methods that take into account the possible zero-inflated nature of the data. The second primary outcome 6MWT is a continuous variable. This data will be stated as means, plus SD, at each time point. To accommodate the repeat measurements for individuals, we will use a generalized linear mixed model to statistically test the hypothesis of both study arms being equal in terms of functional capacity over time.

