All secondary outcomes will be described as means plus SD or median plus IQR, with the data being continuous, and measures for each time point being normally and non-normally distributed respectively. Categorical parameters will be described as number plus percentage per time point. Statistical methods will include t-test and the Mann-Whitney U test for continuous parameters, distributed either normally or not normally respectively, at a single postoperative time-point. Categorical outcomes will be analyzed with Chi-square testing or regression analysis (logistic, ordinal or nominal, depending on the definition of the parameter) for single time points. The size of the sample will be calculated on the basis of the primary aim: the reduction of postoperative complications as determined with the CCI score. With our population variables, the CCI mean is 10.4 (SD 14), and the target reduction is 30%. We use an alpha of 0.05 and power of 0.80 (two-sided test). We expect a dropout rate of 10%. We therefore need 714 patients: 357 in each arm. This gives us sufficient statistical power to demonstrate the expected proportion of difference (55% versus 20%) in the 6MWT between baseline and surgery based on previous studies [14, 27]. Approximately 600 eligible CRC patients undergo surgery in one of the six participating hospitals annually. This implies that we will complete inclusion within two years with the inclusion period being followed by a year of follow-up.

Due to limited clinical data regarding effect size of the primary endpoint – CCI - an interim analysis will be performed. The interim analysis is planned if half of the intended number of subjects have completed the 4 week assessment (i.e. timing of the primary endpoint assessment). The intention of the interim analysis is to terminate the study if there is a statistical significant difference between study arms.

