Limitations of the study should be noted as well. Due to its nature this study is performed non-blinded. This may result in higher dropout rates or an increased activity level in the control group, due to the growing and intuitive understanding of the benefits of exercise training and optimal nutrition. To limit this potential bias of increased activity, we will introduce activity trackers to all patients. We do realize patient characteristics, social circumstances and healthcare facilities will not be the same in all countries. Therefore, we will stratify per participating center. Our international approach of the randomized controlled trial will demonstrate that a worldwide implementation may be possible. In case our multimodal program proves to enhance postoperative outcome, it will be impossible to discover which element of the program attributed most. A large sample size and different outcome measurement will facilitate subgroup analyses, to determine effects of the program within different areas, such as functional capacity, body composition, and quality of life. Also, to allow for comparison of the effects of single modal interventions in this multimodal program. Our large sample size will also give us the possibility to analyze the possible effect differences of an intensive hospital-based prehabilitation program in different patient groups. This way, prehabilitation in the current form can be implemented for patient groups who will benefit the most from intensive hospital-based training. For less high-risk patients, future research could focus on programs in which training is less intensively monitored, such as home-based programs.

Our study investigating prehabilitation is a good example of research in prevention and it will be the first to systematically implement existing knowledge from a variety of different medical specialties and basic science into a four-element multimodal preoperative program for CRC patients with the aim of improving functional capacity and reducing the postoperative complication rate.

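### Randomisation is stratified by site, tumour location and neoadjuvant treatment, but the t-test and Mann-Whitney U named for the primary CCI comparison use none of these factors, so precision may be forgone

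*Protocol article*

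**What the plan says.** Under Randomization, the protocol article states: "Patients will be block randomized with a 1:1 allocation", with allocation "stratified by study sites, tumor location and neoadjuvant treatment". In the limitations part of the Discussion it gives the reason for the centre factor: "We do realize patient characteristics, social circumstances and healthcare facilities will not be the same in all countries". It continues: "Therefore, we will stratify per participating center".

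Under Statistical analysis, three options are left open for testing CCI between the arms. The first is Student's "T-test if data are normally distributed". The second and third come together: "Mann-Whitney U if data are not normally distributed or statistical methods that take into account the possible zero-inflated nature of the data". The same section expects CCI to be right skewed. None of the options is said to use site, tumour location or neoadjuvant treatment, and no adjusted or stratified CCI comparison appears elsewhere in the article.

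The sample size in that section is a comparison of two means without covariates: control mean 10.4, SD 14, a 30% reduction, two-sided alpha 0.05, power 0.80 and 10% dropout, giving 357 patients per arm.

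**The concern.** Blocked allocation within strata keeps the arms balanced on the stratification factors. Variation in CCI between strata therefore largely drops out of the true sampling error of the arm difference. A two-sample t-test does not know this: its standard error is built from the full spread of CCI within each arm, between-stratum variation included. If the strata predict CCI, that standard error is too large, the test rejects a true null hypothesis less often than 5% of the time, and some power is left unused. A Mann-Whitney test is affected in the same direction, through a conservative p-value.

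The article itself expects centres to differ in patients and facilities, and stratifies for that reason. An analysis that then disregards centre does not match the design. What is at stake is precision on a primary outcome, using information already recorded for every randomised patient.

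**Working it through.** **Inputs from the Statistical analysis section.** Control mean 10.4, SD 14 and a 30% reduction, so the difference is 0.30 × 10.4 = 3.12. Two-sided alpha 0.05, power 0.80, dropout 10%, 357 per arm. Six participating hospitals.

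**Input not in the article.** The share of CCI variance explained by the three factors, R². It is assumed here to lie between 0 and 0.20.

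**Step 1: the plan's own figure.** n per arm = 2 × (1.96 + 0.8416)² × 14² / 3.12² = 316.1, so 317. Allowing for dropout, 317 / 0.90 = 352.2, so 353 per arm and 706 in total. The stated 714 is within about 1% of this. The sample size is thus an unadjusted two-mean calculation that uses the full SD of 14.

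**Step 2: evaluable patients.** 357 × 0.90 = 321 per arm, 642 in total. The expected test statistic is Z = (3.12 / 14) × √(321 / 2) = 2.823.

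**Step 3: the two standard errors.** The unadjusted t-test reports 14 × √(2/321). Under stratified allocation the true standard error is about 14 × √(1 − R²) × √(2/321). Writing Φ for the standard normal distribution function:

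- type I error of the unadjusted test = 2 × [1 − Φ(1.96 / √(1 − R²))]
- power of the unadjusted test = Φ((2.823 − 1.96) / √(1 − R²))
- power of the adjusted test = Φ(2.823 / √(1 − R²) − 1.96)
- width of a t-test interval relative to the adjusted one = 1 / √(1 − R²)

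For R² = 0.05, √(1 − R²) = 0.9747. This gives a type I error of 2 × [1 − Φ(2.011)] = 4.4%, unadjusted power Φ(0.886) = 81.2%, and adjusted power Φ(0.937) = 82.6%.

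| Assumed R² | Type I error, unadjusted | Power, unadjusted | Power, adjusted | Excess width of a t-test interval |
|---|---|---|---|---|
| 0 | 5.0% | 80.6% | 80.6% | 0% |
| 0.02 | 4.8% | 80.8% | 81.4% | 1.0% |
| 0.05 | 4.4% | 81.2% | 82.6% | 2.6% |
| 0.10 | 3.9% | 81.9% | 84.5% | 5.4% |
| 0.20 | 2.8% | 83.3% | 88.4% | 11.8% |

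In CCI points, the 95% half-width is 1.96 × 14 × √(2/321) = 2.17 unadjusted. Adjusted, it would be 2.14, 2.11, 2.06 and 1.94 for R² of 0.02, 0.05, 0.10 and 0.20.

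**Step 4: check by simulation.** The check used 3,000 trials per setting, 642 patients, 24 assumed strata (6 × 2 × 2), blocks of 4 and normal outcomes. At R² = 0.10 the type I error was 3.9% unadjusted and 5.0% adjusted, and power was 82.1% and 84.7%. At R² = 0.20 the type I error was 2.9% and 4.9%. These agree with the formulas. The simulation compared means; it did not model skewed or zero-inflated CCI, and it gives no figure for Mann-Whitney.

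**The case against.** **Much of the case against stands.**

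- A reader might infer that every planned CCI analysis ignores the strata. The text does not go that far. Methods for zero-inflated data are often regression models that can carry covariates, and the expected skewness makes the t-test the least likely choice. The statement holds for the two named tests; for the third option one can say only that the factors are not mentioned.
- A reader might infer that a reported confidence interval will be wrong. The article plans summaries and tests for CCI and names no interval, and Mann-Whitney gives none for a mean difference. The widths above describe only an interval that someone might take from the t-test.
- A reader might infer that the trial is underpowered or at risk of false positives. Neither follows. The sample size used the full SD, so unadjusted power is at or above 80% throughout the table, and the error is on the conservative side.
- R² is assumed. If the strata do not predict CCI, nothing is lost. One ERAS guideline applied in all centres (Study outline) would tend to limit differences between centres.
- The stated motive for stratifying by centre is that centres differ, which is a reason of balance. Stratified allocation delivers balance whatever the analysis, and no efficiency aim is stated.
- The same criticism cannot be made of the six-minute walk test. The article names a mixed model without listing covariates, and that detail may properly sit in the analysis plan.

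**One objection does not carry.** It can be said that covariates belong in an analysis plan that is not shown. For CCI, however, the article is not silent: it names two specific two-sample tests, and these do not use the factors of its own randomisation. An analysis plan that adjusted would have to depart from them.

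**Conclusion.** The mismatch between stratified allocation and the two named CCI tests is in the text, and its direction is conservative. Its size cannot be fixed from the article. Over an assumed R² of 0 to 0.20, the true type I error of the unadjusted t-test runs from 5.0% down to 2.8%, and the power forgone runs from nothing to about 5 percentage points. At R² of 0.05 to 0.10 the loss is roughly 1.4 to 2.7 points.

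These figures assume 321 evaluable patients per arm, near-complete balance within strata, a comparison of means, and adjustment terms that capture the stated share of variance. The effect estimate is not biased and the planned power is not undermined. This is an opportunity to gain precision at no cost; it does not threaten the validity of the trial.

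**What to change.** Name one primary CCI analysis that includes the three stratification factors. An example is a linear model for CCI with arm, site, tumour location and neoadjuvant treatment as main effects and robust standard errors. It estimates the mean difference on which the sample size is based. If a rank test is kept, use its stratified (van Elteren) form. If a zero-inflation method is chosen, state that it contains the same factors. The unadjusted test can stay as a sensitivity analysis. Settle this before any comparison of the arms, including the interim analysis.

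The cost is a change of wording and about 7 parameters (5 for six sites, 1 for tumour location, 1 for neoadjuvant treatment) on roughly 640 patients. That count assumes two levels for each of the last two factors, which the article does not state. No extra patients, visits or data are needed, because the factors are recorded at randomisation.
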